1.0 STUDY OBJECTIVES

- 1. Primary Objective
     1. Determine the effect of pentoxifylline 400mg po tid given for 8 weeks on brachial artery FMD in HIV-infected subjects not currently requiring antiretroviral therapy and with CD4 cell counts ≥ 350/µL.
  2. Secondary Objectives
     1. Evaluate the safety and tolerability of pentoxifylline 400mg po tid given over 8 weeks in HIV-infected subjects not currently requiring antiretroviral therapy and with CD4 cell counts ≥ 350/µL.
     2. Determine the effect of pentoxifylline 400mg po tid given for 4 weeks on brachial artery FMD in HIV-infected subjects not currently requiring antiretroviral therapy and with CD4 cell counts ≥ 350/µL.

- - 1. Evaluate the effects of pentoxifylline 400mg po tid on serum MCP-1, sVCAM-1, IP-10, MMP-9, TIMP-1, PAI-1 active, hsCRP, fasting lipoprotein fractions/triglycerides, and peripheral blood immune activation (percentage of CD8+/CD38+/HLA-DR+ T cells) and correlate these changes with changes in FMD.

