1. STATISTICAL CONSIDERATIONS AND DATA MANAGEMENT

9.1 General Considerations

For all analyses, an intention-to-treat (ITT) approach will be used. That is, study results will be analyzed by the treatment groups to which subjects are randomly assigned, regardless of compliance in taking the medication, adherence to the protocol, and completion of the study. This trial will be a double-blind, randomized, placebo-controlled, two parallel group study. Statistical significance will be considered if two-sided p-values are less than 5%. SAS version 9.1 will be used for all statistical analyses. The software PASS was used for sample size calculation.

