9.2 Sample Size Justification

The primary endpoint is change in FMD from baseline to week 8. We used our preliminary data for estimating the detectable difference (Δ) and standard deviation for changes in FMD after 8 weeks with PTX. In the 7 subjects who completed the week 8 visit, an absolute mean (SD) improvement of 4.8% (1.34%) in the change in FMD at week 8 was observed. The 95% confidence interval was 3.5−6.0%. The correlation between week 0 FMD and week 8 FMD was 0.88. We used a very conservative approach, that is, the lower 95% confidence limit for a minimum detectable difference and assumed no change in FMD on average for the placebo group. We also used a conservative approach for estimating the standard deviation in the change in FMD. Our pilot study on 17 HIV positive patients not on cART showed a variability of 2.21 in baseline FMD. Assuming a correlation of 0.30 between week 0 and week8 FMD, we estimated the variability to be 2.62 for the change in FMD which is much higher than the variability we observed in the PTX study.

The sample size was determined based on a two-sample, independent, two-tailed t-test with 5% type I error. Samples sizes were adjusted for an estimated 20% dropout rate. A sample size of 10 per group will have at least 80% power to detect a difference in FMD of at least 3.5% assuming a common standard deviation of 2.62. To adjust for a possible 20% dropout rate, we will recruit 13 per group. The Figure below is a power curve demonstrating the ability to detect various magnitudes of treatment difference assuming a common SD of 2.62.

If a subject withdraws prior to study entry, this subject will be replaced. We expect up to 50 potential subjects will need to be screened to meet the target of 26 randomizations. If we find that the drop-out rate for those on study is greater than the anticipated 20%, then we will replace sufficient numbers of subjects so that the dropout rate is no longer greater than 20%.

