#### 9.3.2 Primary Endpoint Analysis

#### The primary outcome is the change in FMD at week 8 of post treatment from baseline. An analysis of covariance (ANCOVA) model will be used to compare the effect of intervention on this outcome variable. The model will include an indicator variable for intervention, baseline FMD, and other potential covariates, including CD4 cell count, HIV-1 RNA level (viral load), age, sex, race, and BMI. We will include covariates one at a time while keeping the intervention and baseline FMD. All covariates except baseline FMD will be excluded from the model if they have insignificant association with the change in FMD. If the response variable does not follow a normal distribution, an appropriate transformation will be used to approximate a normal distribution. The assumption of the constant variance will also be tested, and a transformation will be used if this assumption is violated.

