9.3.3 Secondary endpoints analyses

The secondary endpoints are the change in FMD at week 4 and the changes in plasma levels of MCP-1, sVCAM-1, IP-10, fasting lipids, HOMA-IR, CD4 cell count, activated CD8 cell proportions, and HIV-1 RNA level at week 8 from baseline. The secondary analyses will be in exploratory nature and will primarily be used for hypothesis generation. All the secondary outcomes will be analyzed by the same statistical methods as for the primary endpoint. To analyze how the changes in secondary outcomes correlate with changes in FMD, Spearman Rank correlation will be used.

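### Section 9.3.3 does not say how the Spearman correlations handle treatment arm; if the arms are pooled and PTX shifts both FMD and a marker, the two changes tend to correlate without any within-arm link

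*Combined protocol and SAP*

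**What the plan says.** The last of the secondary objectives in section 1.0 is to evaluate what PTX does to a list of markers "and correlate these changes with changes in FMD". Section 9.3.3 supplies the method: "To analyze how the changes in secondary outcomes correlate with changes in FMD, Spearman Rank correlation will be used". Neither place says whether the two arms are pooled, analysed separately or adjusted for.

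Two neighbouring statements bear on this. Section 9.3.3 also says: "All the secondary outcomes will be analyzed by the same statistical methods as for the primary endpoint". That method is the ANCOVA of section 9.3.2, of which the plan says: "The model will include an indicator variable for intervention, baseline FMD, and other potential covariates". The arm indicator therefore applies when each marker is analysed on its own as an outcome; the Spearman correlation is a separate step with no model attached. Section 9.3.3 also gives the status of this work: "The secondary analyses will be in exploratory nature and will primarily be used for hypothesis generation".

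**The concern.** In a randomized two-arm trial, two variables that the treatment shifts will differ together between arms. Pooling the arms turns that shared shift into a correlation, even if knowing a subject's marker change tells us nothing about that subject's FMD change once the arm is known.

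The two conditions for this are ones the trial anticipates. Section 2.1 hypothesises that PTX improves FMD more than placebo does. Section 3.1 describes sVCAM-1 and IP-10 as markers that PTX affected in the pilot, and Table 1 in section 2.3.3 shows median changes of -9% (p=0.05) and -28% (p=0.02) for them. The PTX pilot had a single treated group, so the problem could not arise there; the placebo arm introduces it.

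What is at stake is interpretation. A pooled correlation would tend to favour whichever markers PTX moves, and could be read as pointing to a pathway when it only restates that PTX moved both quantities.

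**Working it through.** **Inputs from section 9.2.** Baseline FMD SD 2.21; correlation between week 0 and week 8 of 0.30; detectable difference 3.5 points; SD of change 2.62; no mean change on placebo; 10 evaluable per group, 13 recruited; pilot mean change 4.8. Section 9.1 gives the threshold, two-sided 5%.

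**The plan's own figures reproduce.** SD of change = 2.21 × √(2 × (1 − 0.30)) = 2.615, against the stated 2.62. Exact t-test power for 3.5 points with SD 2.62 is 75.8% at 9 per group and 80.6% at 10, so 10 is right. With 20% dropout, 10/0.80 = 12.5, rounded up to 13. The documents give no figure for the correlation analysis.

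**Effect sizes in SD units.** FMD: 3.5/2.62 = 1.34 as planned; 4.8/2.62 = 1.83 at the pilot mean. Markers: the pilot gives only median percentage changes and p-values, so shifts of 0 to 2 SD are assumed.

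**Large-sample check.** With equal arms, no within-arm correlation, and shifts dx (marker) and dy (FMD), the pooled Pearson correlation is

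r = (dx·dy/4) / √((1 + dx²/4)(1 + dy²/4)).

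For dx = dy = 1.336, dx·dy/4 = 0.446 and r = 0.446/1.446 = 0.31. If either shift is zero, r = 0.

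**Simulation.** There were 40,000 trials per cell. Marker and FMD changes were normal and independent within arm. The pooled Spearman was tested by t = r√(df/(1 − r²)) with df = N − 2. The partial Spearman given arm was (r_xy − r_xa·r_ya)/√((1 − r_xa²)(1 − r_ya²)) with df = N − 3. The Monte Carlo standard error is at most √(0.25/40,000) = 0.25 percentage points. Signs are dropped; a marker that falls as FMD rises gives a negative rho of the same size.

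FMD shift 1.34 SD:

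| Marker shift (SD, assumed) | Large-sample r | Mean pooled rho | p<0.05 pooled, 10 per arm | p<0.05 pooled, 13 per arm | p<0.05 adjusted for arm (10; 13) |
|---|---|---|---|---|---|
| 0 | 0 | 0.00 | 5.1% | 5.1% | 5.0%; 5.0% |
| 0.5 | 0.135 | 0.14 | 8.9% | 10.4% | 5.1%; 5.0% |
| 0.8 | 0.206 | 0.21 | 14.4% | 18.3% | 4.8%; 5.2% |
| 1.0 | 0.248 | 0.26 | 19.7% | 25.1% | 5.2%; 4.8% |
| 1.34 | 0.309 | 0.32 | 29.1% | 37.6% | 5.0%; 5.2% |
| 2.0 | 0.393 | 0.41 | 47.0% | 59.0% | 5.0%; 5.0% |

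At the pilot FMD shift of 1.83 SD, marker shifts of 0.5 to 1.34 SD give 11.0 to 43.1% at 10 per arm and 13.2 to 54.5% at 13 per arm. If PTX does not move FMD, the pooled rate stays at 4.9 to 5.2% whatever the marker does. Ranking within arm also holds the rate at 4.7 to 5.2% in every cell, and using the PTX arm alone gives 5.2 to 5.6%.

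**The case against.** The strongest reply is that the plan never says the arms will be pooled. The objective speaks of the effects of PTX and then of correlating these changes, which could mean changes among treated subjects; the pilot looked for correlations with FMD response within one treated group. A PTX-arm-only correlation is free of this artefact. This part stands: pooling is inferred, and what can be shown is that the plan is silent on arm. Pooling is still the plainer reading, because section 9.3.3 names no subset and section 9.1 applies intention-to-treat to all analyses.

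Second, the plan calls these analyses exploratory, and the primary analysis and sample size do not depend on them. That stands and limits the weight of the point. It does not remove it, because an exploratory correlation that favours markers moved by treatment is a poor source of hypotheses.

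Third, a reader might infer that this is the trial's only mechanistic evidence. The documents do not support that. Every secondary endpoint is also compared between arms by ANCOVA. In section 2.3.3 the sponsor inferred the likely pathway from the significance of the marker changes, not from correlations, and noted that blood markers may miss direct effects on the endothelium. Nowhere does the plan say that a correlation will be reported as mediation.

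Fourth, large marker shifts are plausible for only a few of the listed outcomes. In the pilot, viral load did not change, MCP-1 moved by a median of 1.9% (p=1.0), and no lipid or metabolic measure changed apart from a non-significant fall in triglycerides. This also stands.

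**Conclusion.** The point holds as a conditional one. Section 9.3.3 leaves the handling of arm unstated; if the arms are pooled and PTX shifts both FMD and a marker, an association appears that treatment assignment alone explains. At the planned FMD effect, and for assumed marker effects of 0.5 to 1.34 SD, a nominal 5% test rejects in about 9 to 29% of trials at 10 per arm and 10 to 38% at 13 per arm. These figures rest on normal changes, equal variances, no within-arm link and marker effects that the documents do not supply.

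It would go too far to say that any marker moved by PTX will correlate with FMD. PTX must move FMD as well. Even then the induced rho is moderate, and in most trials over the 0.5 to 1.34 SD range at the planned FMD effect it would not reach significance. The matter is worth settling before the data are analysed, but it does not touch the primary conclusion.

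**What to change.** Replace the correlation sentence in section 9.3.3 with wording such as: *Exploratory associations between change in each secondary outcome and change in FMD will be estimated by partial Spearman correlation adjusted for treatment arm, with scatter plots by arm. Any unadjusted pooled coefficient will be labelled descriptive and as including the treatment effect.* If the sponsor instead intends within-arm or PTX-arm-only correlations, section 9.3.3 should say so; either also avoids the artefact.

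The cost is one sentence, a small program change and one degree of freedom: 17 instead of 18 with 20 evaluable subjects, or 23 instead of 24 with 26. Data collection, sample size and the primary analysis do not change. The text should add that adjustment for arm removes this artefact but does not by itself establish that a marker mediates the effect on FMD.

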9.3.4 Randomization

26 HIV-infected patients not on cART will randomly be assigned to either the placebo or the pentoxifylline groups. The study statistician will generate a computerized randomization plan that will employ a certain block size for this trial. The block size will be known only to the statistician to maximize blinding for the subject and other study investigators.

9.4 Study Population

The subjects for these studies will be recruited from the HIV outpatient clinics at Indiana University and Wishard Hospitals. A survey of these clinics (total active clinic population of 2000 patients) suggest that at least 150 patients are not currently receiving cART and have CD4 counts >350cells/µL. Even accounting for other criteria that may exclude potential subjects, we expect that there should be no difficulties in enrolling the required 26 total subjects for this trial.

9.5 Study Duration

Based on the enrollments rates into our pilot trials, we expect to enroll 2 subjects per month. Therefore, the enrollment period will be approximately 13 months. The study period for each subject will be no more than 11 weeks (screening phase of 3 weeks and main visit phase of 8 weeks). Thus, the study durations will be 16 months. Including an additional 6 months to account for any unlikely difficulties in enrollment or trial procedures will raise this estimate to 22 months.

9.6 Data Management

A comprehensive web-based data management system will be developed for this study which will allow controlled entry through the internet. All data will be entered and stored in a password-protected Microsoft SQL Server 2005 database housed on a secured server separate from the web-server in the Division of Biostatistics. Server-side scripting hides the database calls from the web clients, obfuscating the data storage location.  An experienced Database Administrator provides database creation, daily backup, and installation of security patches.

A unique identifier will be assigned to each study participant and their associated study specimens. Patient identifiers will be located only within the subject’s study file in a separate, locked cabinet within the Infectious Diseases Research Clinic (IDRC) at University Hospital. Hardcopies of laboratory source records will also be stored in a locked file cabinet. All entryways to the IDRC are secured by padkey codes. Initial screening, consenting of potential subjects, and data abstraction and recording will be completed by the primary investigator with assistance from the research study nurse coordinators from the IDRC.

The data management system will facilitate quality control efforts, prevent entry of erroneous values, provide warnings for possible outliers, generate missing data reports, track subjects and samples, and assist in the preparation of data for statistical analysis. All data will be reviewed and processed through multiple verification and edit checking programs post entry to ensure data quality.

To facilitate data harmonization and ensure consistency with other research sites, every effort will be made to coordinate the collection and storage of data. The data managers will work with the Data Coordinating Center (DCC) to establish standards for terminology, data elements, and methodologies. Electronic data and research specimens will be provided to the DCC as needed.

1. HUMAN SUBJECTS RESEARCH AND PROTECTION

10.1 Investigator Training

All Indiana University personnel involved with this application have successfully completed the training and examination involved with the Indiana University Human Subjects Protection Course.

10.2 Risks to the Subjects

10.2.1 Human Subjects Involvement and Characteristics

- HIV-infected subjects will be recruited to participate in two randomized, placebo-controlled clinical trials investigating the efficacy of oral pentoxifylline to improve endothelial function.
  - Subjects must be at least 18 years of age, have documented HIV infection, and have not been hospitalized or untreated for severe illness/infection within 14 days prior to screening. A total of 26 subjects will be randomized.
  - The primary inclusion criteria are no receipt of cART within 6 months and no anticipated need for cART during the course of the trial. The chief exclusion criteria include known vascular disease, renal disease, diabetes, and treatment for hypertension or dyslipidemia at screening.
  - Potential subjects will be recruited from the Indiana University Hospital and Wishard Hospital infectious diseases outpatient clinics (both hospitals are affiliated with the Indiana University School of Medicine in Indianapolis). All procedures will occur in the Indiana Clinical Research Center at Indiana University Hospital.
- The only potential vulnerable subject population that may be included for these trials include children of at least 18 years of age.

10.2.2 Sources of Materials

- All data for this study will be obtained only after informed consent is provided by each subject. Existing medical records will be reviewed for demographics, medical diagnoses, and medications. Urine samples will be obtained for assessment of pregnancy (females only), dipstick measurements, and quantitative proteinuria/albuminuria levels. Serum/plasma samples will be obtained for testing for renal function, fasting metabolic parameters, hepatitis B and C co-infection status, HIV-1 RNA levels, CD4 cell counts, pentoxifylline levels, and inflammatory markers. Whole blood will also be collected for measurement of activated CD8 cells. Urine, serum, plasma, and cells will be obtained for deposition at the DCC and also at IU for future studies of interest. DNA will not be stored or analyzed for these studies. Ultrasound images from the brachial artery flow-mediated dilation testing will also be collected. Please see DATA SHARING PLAN for additional information regarding distribution of the unique datasets constructed from these studies.
- Results from pertinent medical records and procedures performed for these studies, as outlined above, will be recorded on the human subjects involved in the projects in this application.
- Data will be stored in a password-protected computerized database that will include only the subjects’ study identification number (names and other identifiable information will not be included). Therefore, the SID# will be the only link to the subject. Only the principal investigators, co-investigators, and research personnel who will directly obtain the necessary data will have access to the subject identities. All data obtained for this study will be obtained only after written, informed consent is provided by each subject.
- Records will be reviewed manually. Urine specimens will be obtained via standard clean-catch technique. Blood specimens will be obtained via peripheral venipuncture. Flow-mediated dilation of the brachial artery will be measured using high frequency ultrasound with images downloaded to a secure, encrypted electronic database. These data will be collected solely for the purpose of the proposed research projects.

10.2.3 Potential Risks

- There are minimal risks to the subjects enrolled in the proposed research. The first is the potential loss of subject confidentiality. The second consists of the risks associated with blood drawing/needle sticks, which include pain, bruising, infection, and phlebitis. The amounts of blood to be drawn at screening and at each main study visit are 15cc (one tablespoon) and 45cc (three tablespoons), respectively. The total amount of blood to be obtained would be approximately 150cc (10 tablespoons) over at least 11 weeks. The primary risks associated with the use of pentoxifylline are gastrointestinal (nausea, vomiting, dyspepsia), flushing, and dizziness. PTX is a Pregnancy Category C drug and is found in breastmilk. There are no known or potential interactions with antiretroviral medications or commonly used therapies in the HIV-infected population. Nevertheless, we will carefully monitor CD4 counts and HIV-1 viral loads to assess for any potential worsening of immunologic/virologic status for those randomized to PTX during these studies and will be evaluated carefully by the DSMB. The primary risks associated with nitroglycerin administration as part of the brachial artery testing are headache and transient hypotension. NTG may also infrequently cause the sensation of flushing of the skin and rash. There may also be moderate pain associated with the inflation of forearm cuff as part of the brachial reactivity testing.
- The principal alternative to these procedures would be not to participate in the research.

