4.3 Co-enrollment Guidelines

Co-enrollment into other studies will be permitted provided no drugs prohibited on this study will be given in the other study/ies and that the required blood draws do not exceed safe limits when combined with those for this study.

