6.2.1 Screening Evaluations

There will be one screening visit to determine eligibility. This must be completed within 21 days of entry (Week 0/Day0 Main Study Visit).

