6.2.2 Main Study Evaluations

There will be three main study visits where blood and urine samples will be obtained, anthropometrics performed, and brachial artery ultrasound measurements will be performed. The Week 4 visit will occur as near to Day 28 after entry as possible, but can occur as late as 42 days after entry. The Week 8 visit will occur as near to Day 56 after entry as possible, but can occur as late as 70 days after entry. Each subject will continue to take study drug/placebo until the final study visit is completed.

- - 1. Study Discontinuation Evaluations

Study subjects who complete the entry (Week 0/Day 0) procedures and have taken at least two weeks of study drug but thereafter notify the study team that they will terminate their involvement prior to the Week 4 visit will have their Week 4 evaluations performed as soon as possible after the time of notice of termination. Subjects who notify the study team that they will terminate their involvement prior to the Week 8 visit and have taken at least 6 weeks of study drug will have their study Week 8 evaluations performed as soon as possible after the time of notice of termination. Subjects who notify the study team that they will terminate their involvement within two weeks after the Week 0 or Week 4 visit evaluations have been completed will have no further evaluations performed.

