6.3.8.12 Specimen Collection, Processing, Labeling, and Storage for Specimens for Future Analysis

Plasma

- Collection:
  - For plasma #1, collect ONE (1) 7.0-mL, purple-top EDTA tube, FILL COMPLETELY (for possible additional HIV-1 RNA PCR testing). Complete processing within 6 hours of collection.
  - For plasma #2, collect ONE (1) 7.0-mL, purple-top EDTA tube, FILL COMPLETELY. After collection of blood, gently invert the tube 10 to 15 times and keep upright at room temperature until centrifugation. Keep refrigerated at 4oC after draw if unable to centrifuge immediately.
  - For plasma #3, collect an additional ONE (1) 7.0-ml 3.2% buffered Sodium citrate (SCI) tubes, fill completely (for storage). Mix gently by inverting 8 times immediately after filling. Do not shake the tube as this will break down fibrinogen in the sample. COMPLETE PROCESSING W/IN 1 HR OF COLLECTION.
- Processing:
  - For plasma #1 tube, spin at 800 x *g* for 10 minutes at room temperature. Plasma should be carefully removed from each tube, placed in a sterile polypropylene conical centrifuge tube and centrifuged again (at 800 x *g*) at room temperature for 10 minutes to completely remove platelets and cell debris. Prepare at least 3 aliquots (each containing 1.0-mL) from each 7mL EDTA tube and freeze at -80°C.
  - For plasma #2 tube, spin 3000 x *g* for 10 minutes at 4oC. Prepare at least 3 total aliquots containing at least 1.0-mL of plasma each and freeze at 80C within 4 hours of collection.
  - For plasma #3 tube, spin at 1500 x *g* for 15 minutes at room temperature. Prepare at least 3 total aliquots containing at least 1.0-ml of plasma each and freeze at –80ºC within 60 minutes of collection.
- Labeling: Label on each aliquot the protocol-subject number, date, specimen type “HIV-PLA”, “E-PLA”, and “S-PLA” for tube number 1, 2, and 3, respectively.

Serum

- Collection: Collect FOUR (4) 7.0-mL red-top tubes without additive (for glucose, insulin, lipids, inflammatory markers, pentoxifylline levels, and other future studies) at room temperature. Let blood clot 30 minutes at room temperature in vertical position.
- Processing:

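### The blood volumes stated in section 10.2.3 (45 cc per main visit, about 150 cc in total) are lower than the plan's own tube list and laboratory schedule imply

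*Combined protocol and SAP*

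**What the plan says.** Section 10.2.3 (Potential Risks) gives the volumes at screening and at each main visit as "15cc (one tablespoon) and 45cc (three tablespoons), respectively". It then states: "The total amount of blood to be obtained would be approximately 150cc (10 tablespoons) over at least 11 weeks".

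The visit counts are in sections 6.2.1 and 6.2.2: "There will be one screening visit to determine eligibility" and "There will be three main study visits where blood and urine samples will be obtained".

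Section 6.3.8.12 lists the tubes for stored specimens. For plasma: "For plasma #1, collect ONE (1) 7.0-mL, purple-top EDTA tube, FILL COMPLETELY"; "For plasma #2, collect ONE (1) 7.0-mL, purple-top EDTA tube, FILL COMPLETELY"; and a third 7.0-mL tube, with citrate, which must also be filled. For serum: "Collect FOUR (4) 7.0-mL red-top tubes without additive".

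Other blood is described elsewhere:

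- Section 6.3.8.11 sends safety bloods separately to the clinical laboratory for immediate analysis and calls for fresh whole blood in EDTA tubes for the activated CD8 measurement.
- The Schedule of Events (6.1) marks hematology, liver tests, creatinine, CD4/CD8 counts and HIV-1 RNA at all three main visits, hepatitis serologies at entry, and flow cytometry at Weeks 0 and 8.
- The schedule also marks frozen marker samples at screening. Section 3.2 confirms this, because screening and baseline marker results are to be averaged.

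Section 4.3 permits co-enrollment provided, among other things, that "the required blood draws do not exceed safe limits when combined with those for this study".

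**The concern.** The risk section and the specimen section describe the same visits and give different amounts of blood. The stored-specimen tubes alone come to more than the whole draw stated for a main visit, before any blood for same-day tests is counted.

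The volume is a stated research risk, and section 10.3.2.2 relies on it in saying that the amount is well within blood-donation standards. It is also the only volume in the protocol that could be entered into the co-enrollment check. Anyone who takes 150 cc as this trial's share of a combined draw starts from too low a number. No endpoint, sample size or analysis depends on it.

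**Working it through.** **Inputs**

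- Stated draws: 15 cc at screening, 45 cc per main visit, about 150 cc in total (10.2.3).
- Visits: one screening, three main (6.2.1, 6.2.2).
- Stored-specimen tubes: three plasma and four serum, each 7.0 mL (6.3.8.12). That section does not tie the list to a visit. The schedule marks both frozen-sample rows at Weeks 0, 4 and 8, so the list is read as one set per main visit.
- Safety, virology and flow tubes: no volume stated.

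**Step 1. The stated total.** 15 + 3 x 45 = 150 cc. It reproduces exactly, so it carries any error in the 45 cc.

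**Step 2. Stored tubes at one main visit.** 3 x 7.0 + 4 x 7.0 = 21 + 28 = 49 mL. Against 45 cc this is 4 mL more (4/45 = 9%).

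**Step 3. Total with the stated screening draw.** 3 x 49 + 15 = 147 + 15 = 162 mL, and 162/150 = 1.08. Nothing is yet counted for safety, CD4/CD8, viral-load, hepatitis or flow tubes at the main visits.

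**Step 4. Allowance for those tubes (assumption).**

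| Assumed addition | Total | Relative to 150 cc |
| --- | --- | --- |
| 10 mL per main visit, all tests | 162 + 30 = 192 mL | +28% |
| 20 mL per main visit, all tests | 162 + 60 = 222 mL | +48% |
| 10 mL per main visit, plus 3 mL for flow at Weeks 0 and 8 | 162 + 30 + 6 = 198 mL | +32% |
| 20 mL per main visit, plus 7 mL for flow at Weeks 0 and 8 | 162 + 60 + 14 = 236 mL | +57% |

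The last two rows follow the schedule more closely, since flow is not done at Week 4.

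**Step 5. Could partly filled serum tubes rescue 45 cc?** The plasma tubes must be full: 21 mL. That leaves 45 - 21 = 24 mL, or 6 mL in each of four serum tubes, and nothing for any other test. The serum instructions also ask for at least ten 1.0-mL aliquots. If serum is 40 to 50% of blood volume (assumption), that takes 20 to 25 mL of blood. Stored specimens then need 41 to 46 mL, which leaves at most 4 mL for every other tube.

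**Step 6. Screening.** The 15 cc must cover hematology, liver tests, creatinine, CD4/CD8 and the frozen marker samples. The number of marker tubes is not stated. One 7-mL tube would leave 8 mL for the eligibility tests, and two would leave 1 mL.

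**The case against.** The strongest reply is that the stated volumes are rounded and the tube volumes nominal. Section 10.2.3 counts in whole tablespoons of 15 cc and calls the total approximate. At 49/15 = 3.3 tablespoons, the stored tubes round to three. Only the plasma tubes carry an instruction to fill. This stands for the 4 mL excess taken alone. It does not stretch to the safety, CD4/CD8, viral-load and flow blood as well, as step 5 shows.

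The documents do not support several stronger readings that a reader might infer:

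- **That stored tubes alone exceed 150 cc.** Over the three main visits they total 147 mL, just under it. The total passes 150 only once screening blood is counted.
- **That a full set of seven tubes is also drawn at screening, giving 4 x 49 = 196 mL.** The schedule marks only the marker row at screening. The row for future studies is blank there.
- **That the second glucose and insulin sample in Appendix I is extra blood.** The four serum tubes are already designated for glucose and insulin, so it may lie within them.
- **That participants were given a wrong figure.** The consent pages are not available for review.
- **That the volume is unsafe, or that a co-enrollment decision would change.** No limit is stated anywhere, and section 4.3 does not cite the 150 cc.

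The documents also do not show which side is in error: the risk figure may be low or the tube list too long.

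**Conclusion.** The contradiction is real but minor. For the procedures as listed, 45 cc per main visit is too low: the stored-specimen tubes are nominally 49 mL and further blood is scheduled at every main visit. The 150 cc total inherits the shortfall and becomes at least 162 mL (+8%), given nominal tube volumes, one stored set per main visit and the stated 15 cc at screening. The range of about 192 to 222 mL (+28% to +48%) rests on an assumed 10 to 20 mL per main visit for the remaining tubes. The true figure cannot be derived from the documents. Whether 15 cc suffices at screening is also open. What is established is a risk figure that is wrong as written, with no demonstrated safety problem and no bearing on the trial's results.

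**What to change.** Reconcile sections 6.1, 6.3.8.11, 6.3.8.12 and 10.2.3 with one table of tubes by visit. It should give number and volume for stored plasma and serum, safety laboratories, CD4/CD8, HIV-1 RNA, hepatitis serologies and flow cytometry. It should state how many marker tubes are drawn at screening and whether the second glucose and insulin sample comes out of the four serum tubes.

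Then either restate the per-visit and total volumes in section 10.2.3, or shorten the tube list until 15, 45 and 150 cc are true. Check the consent form and the blood-donation statement in section 10.3.2.2 against the result, and use the corrected total for the check in section 4.3.

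If the volumes are restated, the cost is a wording change in the protocol, and in the consent form if it carries the same figures, with a somewhat less favourable number. Shortening the tube list would instead reduce the stored samples. Neither route touches the primary analysis.
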